**Sample size**

There has been some degree of ambiguity about sample size requirements for feasibility studies and there are no previous studies which have evaluated BA in YPEEP which could be used to guide this estimate. Therefore, our sample size estimation will be based on recommendations from the literature that feasibility studies ought to aim for sample sizes of between 24 and 50 participants [23, 24]. Furthermore, a systematic review of UK registered feasibility studies reported the median sample size with continuous outcome measures to be 30 participants per group [25]. Based on this guidance, our target sample size is 60 participants (30 in each group). This estimate will facilitate the generation of information about sample size requirements for a subsequent full-scale trial and is not intended to be sufficiently powered to detect statistically significant differences in outcomes between groups.

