**Preliminary intervention effects (primary and secondary outcomes)**

The primary outcome will be the assessment of depressive symptoms. The secondary outcome will be the assessment of negative symptoms, overall psychiatric symptoms, medication side effects, and functioning. Outcome measures will be completed at baseline (0 weeks), immediately post-intervention (6 weeks) and 3-months post-intervention.

Depressive symptoms: The depressive symptoms will be measured with Calgary Depression Scale for Schizophrenia (CDSS) [30]. The CDSS is a 4-point Likert type scale (0, absent; 1, mild; 2, moderate; 3, severe) with nine items. It is considered to be a reliable scale, with high internal consistency (Cronbach's alpha= 0.855), and the CDSS is suitable for evaluating symptoms of depression in people at clinical high risk for psychosis [31], including young people [32].

Negative symptoms: The Scale for Assessment of Negative Symptoms (SANS) [33] will be used to assess the negative symptoms of schizophrenia. SANS is 6-point Likert type scale (from 0, none to 5, severe), comprised of five scales each of which assess aspects of negative symptoms; alogia, affective blunting, avolition-apathy, anhedonia-asociality, and attentional impairment. The SANS has demonstrated a high level of reliability, with an overall Cronbach’s alpha ranging from 0.89 to 0.95 and global intraclass correlation coefficient (test-retest reliability) of more than 0.82 in different studies [33-35].

Psychiatric symptoms: The Brief Psychiatric Rating Scale (BPRS) [36] is a 7-point Likert type scale (1, not present-7, extremely severe) which is used to rate psychiatric symptoms such as anxiety, depression, and psychoses. The BPRS has demonstrated good reliability, with overall Cronbach’s alpha value of 0.69 [37] and an overall intra-class correlation of R = 0.78 (p< 0.001) [38].

Medication side effects: The Glasgow Antipsychotic Side-effect Scale (GASS) [39] is 4-point Likert type scale (from 0 point, never to 3 point, everyday) containing 22 items. It is a self-report rating scale which measures an individual’s viewpoint about side effects of antipsychotic medication. The GASS has demonstrated a good test-retest reliability (kappa value=0.72) [39] and internal consistency reliability with Cronbach's alpha ranging from 0.793 to 0.903 [40-42].

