**Data collection and management**

The trained research assistant will facilitate the data collection process. With prior written consent, participant demographic information will be collected through the early psychosis service at the study site. For the primary (depressive symptoms) and secondary outcomes (negative symptoms, overall psychiatric symptoms, medication side effects, functioning), the data will be collected at baseline, 6 weeks post-intervention and 3 months post-intervention respectively. There are no plans for specific activities to promote participant retention other than the BA intervention being facilitated by participants’ regular clinician and by keeping participant burden to a minimum. With participants’ permission, all outcome data will be collected and analysed from participants who discontinue the study or deviate from the intervention protocol.

The qualitative interviews will be audio-recorded and will subsequently be transcribed. The researcher conducting the interview will ensure that there is no patient identifiable information (e.g. names, addresses) on the audio recording. A professional transcription service with appropriate confidentiality and data security policies will be engaged to transcribe digital recordings of the interviews. Transcriptions will be de-identified by the research team to ensure anonymity. Subsequently, audio-recordings will be securely destroyed. Data will be stored securely on the university’s server and files will be password protected. Only the relevant members of the research team will have access to these files. In accordance with NHMRC guidelines for clinical trials, data will be retained for 15 years and then securely destroyed. Data will be managed in accordance with the National Statement on Ethical Conduct in Human Research and the Charles Darwin University Research Data Management Procedures [45].

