**Data analysis**

*Qualitative data analysis*

Qualitative interview data will be content analysed from a phenomenological perspective following Braun and Clarke’s thematic analysis procedure [46]. The planned analysis encompasses the processes of immersion in the data set, line by line coding so to generate a set of preliminary codes, the development of tentative themes, reflection upon and revision of themes as needed before defining and describing finalised themes. The analysis will be inductively-oriented and data-driven. Codes and themes will be validated by an independent researcher at key points in the analysis. NVivo Pro software version 12 will be employed to facilitate the analysis.

*Statistical analyses*

Raw data will be entered and analysed with SPSS (the Statistical Package for the Social Sciences) for Windows, version 26. The demographic characteristics and baseline data measure (mean scores) of all participants will be compared between the two study groups, using Chi-squared test or independent samples t-test to assess the homogeneity of the two groups. The generalized estimating equation (GEE) will be employed to analyse the preliminary effects of BA across the three points (baseline, and 6-weeks and 3-months after intervention) following the intention-to-treat principle, and relevant effect sizes will be calculated. The GEE analysis will account for intra-correlated repeated outcome data and accommodate data missing at random. Feasibility data will be summarized with descriptive statistics. T-tests will be carried out to examine any significant statistical differences between the two arms on primary and secondary outcome measures at both follow-up measurements if the statistical significance of the overall treatment effect was found in the GEE analysis. We will also conduct Chi-squared test or independent samples t-tests (depending on normality of data) to assess significant differences in baseline data measures between participants that discontinue the study and those that adhere to the study protocol/com. In all tests, the level of significance will be set at P values of < 0.05.

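### The CDSS is the declared primary outcome at two follow-ups, but neither visit nor any GEE term is named as the main estimate

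*Protocol*

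**What the plan says.** The section on preliminary intervention effects states that "The primary outcome will be the assessment of depressive symptoms", names the CDSS as the measure, and adds that "Outcome measures will be completed at baseline (0 weeks), immediately post-intervention (6 weeks) and 3-months post-intervention". It ranks neither follow-up above the other.

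The Data collection and management section lists the visits again, also unranked, but words the first follow-up differently: "the data will be collected at baseline, 6 weeks post-intervention and 3 months post-intervention respectively".

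The Data analysis section plans a GEE to "analyse the preliminary effects of BA across the three points (baseline, and 6-weeks and 3-months after intervention"), and says "and relevant effect sizes will be calculated". It then plans t-tests between the arms "at both follow-up measurements if the statistical significance of the overall treatment effect was found in the GEE analysis". On the threshold it says: "In all tests, the level of significance will be set at P values of < 0.05".

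The Sample size section sets 60 participants, 30 per group, and disclaims power for group differences. It says of the target: "This estimate will facilitate the generation of information about sample size requirements for a subsequent full-scale trial". The Study aim and objectives section lists preliminary efficacy among the additional aims, after four feasibility objectives.

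**The concern.** A primary outcome is not fully defined until its time point is given. The arm difference at the end of the BA course measures immediate response. The difference at 3 months measures whether the response lasts. These are different questions and can have different answers. As written, the plan yields a CDSS comparison at each visit plus an overall GEE result, and does not say which of the three is the main finding.

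A statistical analysis plan would normally specify the model for an outcome that the protocol has already fixed. It would not normally choose the primary time point, so an unseen plan does not excuse the gap.

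What is at stake is the efficacy estimate that the pilot hands to the designers of the full trial. If the visit is chosen after the results are known, the reported effect tends to be too large.

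**Working it through.** **1. The plan's own figure.** The target of 60 is 2 × 30, from the median of 30 per group that the Sample size section cites. No effect size, SD, visit correlation or dropout rate is given, so those used below are assumptions.

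**2. Does the GEE precondition control false positives?** Two unconditional tests at 0.05 give 1 − 0.95² = 9.75% if independent. Simulation with 30 per arm (40,000 trials) gives 9.5% to 7.7% for visit correlations of 0.3 to 0.8. With a significant overall effect required first, the chance that a visit t-test is run and is significant under the global null falls to between 0.8% and 4.5%. That range covers three readings of the overall effect: a group-by-time test, a joint test of the two follow-ups, and an average over all three points. The simulation used Hotelling and t-type tests in place of the GEE, whose contrast is undefined. So false positives stay at or below 5%, provided one reading is fixed.

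**3. Does the overall effect supply the main estimate?** Not as written. Suppose the true difference is 0 at baseline and d at both follow-ups.
- Averaged over all three points, the group effect is (0 + d + d)/3 = 0.67d.
- With group-by-time terms and baseline as the reference, the group term is the baseline difference, and the treatment effect lies in two interaction terms, one per visit.
- A joint test of both visits gives a p-value but no single estimate.

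The plan chooses none of these. The precondition also applies to the t-tests only; the effect sizes are to be calculated regardless.

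**4. Size of the selection effect.** For a standardised difference with n per arm, SE ≈ √(2/n) = √(2/30) = 0.258. If two visits have the same true effect and their estimates correlate at ρ, the expected excess of the larger over the true value is SE × √((1 − ρ)/π).

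| ρ (assumed) | √((1 − ρ)/π) | Overstatement (SD) |
|---|---|---|
| 0.3 | 0.472 | 0.12 |
| 0.5 | 0.399 | 0.10 |
| 0.7 | 0.309 | 0.08 |

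The simulation at an assumed true effect of 0.4 SD agrees: the larger estimate exceeded the mean first-visit estimate by 0.126, 0.107 and 0.084. An effect of 0.40 would then be reported on average as about 0.50 (0.48 to 0.52).

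**5. What naming a visit does not cure.** A pre-named, unadjusted contrast still has a 95% half-width of about 1.96 × 0.258 = 0.51 SD. Naming the visit removes selection, not imprecision.

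**6. What baseline adjustment adds.** The planned t-tests ignore baseline CDSS. Adjusting for it multiplies the SE by about √(1 − r²), where r is the correlation of baseline with follow-up (assumed).
- r = 0.3: √0.91 = 0.954, SE about 5% smaller, half-width about 0.48 SD.
- r = 0.7: √0.51 = 0.714, SE about 29% smaller, half-width about 0.36 SD.

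**7. Timing of the first follow-up.** The outcomes section puts it at 6 weeks, immediately after a six-week course. Read literally, the Data collection and Data analysis sections put it 6 weeks after the intervention, which is 6 + 6 = 12 weeks from baseline. These descriptions must be reconciled before that visit can be named as primary.

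**The case against.** The strongest objection is that the plan does have an order. One GEE comes first, and the visit t-tests follow only if it is significant. A reader might infer from the two unranked visits that a significant efficacy result can be taken freely from the more favourable one. The documents do not support that: the precondition holds false positives at or below 5% once its contrast is fixed. This part of the objection stands. It does not tell the reader which estimate is the main one.

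Second, a reader might infer that the full trial will be sized on the larger observed effect and so be underpowered. The Sample size section says only that the pilot will generate information about sample size. That could equally mean the SD, consent or retention. Carrying the larger effect forward is possible, not planned, so no loss of power in the full trial can be charged to this protocol.

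Third, efficacy is an additional objective, power is disclaimed, and no progression rule uses a CDSS contrast. That stands and lowers the severity. It does not remove the gap, because the Protocol itself declares a primary outcome and plans significance tests on it.

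Fourth, the two visits may disagree by chance alone, and naming one does not prevent that. This is correct. The benefit claimed here is limited to removing the selection bias and, through adjustment, to a tighter interval.

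**Conclusion.** The point holds in a limited form. The primary outcome has two follow-ups and no main one. The GEE precondition protects against false positives but leaves both the overall effect and the visit of the effect sizes open, and the visit comparisons ignore baseline CDSS.

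The avoidable overstatement is about 0.10 SD (0.08 to 0.12), and it arises only if the larger visit effect is carried forward. It assumes 30 per arm, complete data, equal true effects at both visits and visit correlations of 0.7 to 0.3. Baseline adjustment would reduce the standard error by about 5% to 29% for an assumed baseline correlation of 0.3 to 0.7. Severity is minor to moderate.

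**What to change.** Before any outcome data are examined, amend the outcomes and Data analysis sections as follows. Blinding of the statistician is not a sufficient deadline, because the research assistants who collect outcomes are unmasked.

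- Name one CDSS follow-up as the main contrast. The end-of-treatment visit is a reasonable choice; the sponsor may justify 3 months instead.
- Estimate it as the baseline-adjusted difference between arms at that visit from the GEE, with baseline CDSS as a covariate rather than as one of the outcome points.
- Report it with a 95% confidence interval whether or not the overall test is significant.
- Report the other visit as secondary, with its interval.
- State that any effect estimate offered for planning the full trial is the pre-named one, shown with its interval.
- Reconcile the descriptions of the first follow-up in the outcomes, Data collection and Data analysis sections.

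The cost is a few sentences, with no new visits or data. The sponsor gives up the freedom to choose the visit afterwards.

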**Data collection and management**

The trained research assistant will facilitate the data collection process. With prior written consent, participant demographic information will be collected through the early psychosis service at the study site. For the primary (depressive symptoms) and secondary outcomes (negative symptoms, overall psychiatric symptoms, medication side effects, functioning), the data will be collected at baseline, 6 weeks post-intervention and 3 months post-intervention respectively. There are no plans for specific activities to promote participant retention other than the BA intervention being facilitated by participants’ regular clinician and by keeping participant burden to a minimum. With participants’ permission, all outcome data will be collected and analysed from participants who discontinue the study or deviate from the intervention protocol.

The qualitative interviews will be audio-recorded and will subsequently be transcribed. The researcher conducting the interview will ensure that there is no patient identifiable information (e.g. names, addresses) on the audio recording. A professional transcription service with appropriate confidentiality and data security policies will be engaged to transcribe digital recordings of the interviews. Transcriptions will be de-identified by the research team to ensure anonymity. Subsequently, audio-recordings will be securely destroyed. Data will be stored securely on the university’s server and files will be password protected. Only the relevant members of the research team will have access to these files. In accordance with NHMRC guidelines for clinical trials, data will be retained for 15 years and then securely destroyed. Data will be managed in accordance with the National Statement on Ethical Conduct in Human Research and the Charles Darwin University Research Data Management Procedures [45].

**Data analysis**

*Qualitative data analysis*

Qualitative interview data will be content analysed from a phenomenological perspective following Braun and Clarke’s thematic analysis procedure [46]. The planned analysis encompasses the processes of immersion in the data set, line by line coding so to generate a set of preliminary codes, the development of tentative themes, reflection upon and revision of themes as needed before defining and describing finalised themes. The analysis will be inductively-oriented and data-driven. Codes and themes will be validated by an independent researcher at key points in the analysis. NVivo Pro software version 12 will be employed to facilitate the analysis.

*Statistical analyses*

Raw data will be entered and analysed with SPSS (the Statistical Package for the Social Sciences) for Windows, version 26. The demographic characteristics and baseline data measure (mean scores) of all participants will be compared between the two study groups, using Chi-squared test or independent samples t-test to assess the homogeneity of the two groups. The generalized estimating equation (GEE) will be employed to analyse the preliminary effects of BA across the three points (baseline, and 6-weeks and 3-months after intervention) following the intention-to-treat principle, and relevant effect sizes will be calculated. The GEE analysis will account for intra-correlated repeated outcome data and accommodate data missing at random. Feasibility data will be summarized with descriptive statistics. T-tests will be carried out to examine any significant statistical differences between the two arms on primary and secondary outcome measures at both follow-up measurements if the statistical significance of the overall treatment effect was found in the GEE analysis. We will also conduct Chi-squared test or independent samples t-tests (depending on normality of data) to assess significant differences in baseline data measures between participants that discontinue the study and those that adhere to the study protocol/com. In all tests, the level of significance will be set at P values of < 0.05.

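### The protocol credits plain GEE with handling data missing at random, which it does not do in general, and the follow-up t-tests have no such protection

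*Protocol*

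**What the plan says.** All references are to the protocol; no SAP is at hand.

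- **Model (Data analysis, Statistical analyses).** "The generalized estimating equation (GEE) will be employed to analyse the preliminary effects of BA across the three points", "following the intention-to-treat principle, and relevant effect sizes will be calculated".
- **Missing data (same section).** "The GEE analysis will account for intra-correlated repeated outcome data and accommodate data missing at random". The sentence carries no condition, and the section names no working correlation, weighting, imputation or likelihood-based model.
- **Follow-up comparisons (same section).** If the GEE shows a significant overall treatment effect, the arms are compared by t-test at each of the two follow-ups. "In all tests, the level of significance will be set at P values of < 0.05".
- **Dropout check (same section).** Participants who discontinue are compared with those who adhere, on baseline measures only.
- **Retention (Data collection and management).** "There are no plans for specific activities to promote participant retention other than the BA intervention"; the sentence goes on to say that the regular clinician delivers it and that burden is kept low. Outcome data from participants who discontinue will be collected, with their permission.
- **Size (Sample size).** "our target sample size is 60 participants (30 in each group"), and the sample "is not intended to be sufficiently powered to detect statistically significant differences in outcomes between groups".

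**The concern.** The sentence is a positive claim about a method, and the claim is wrong as a general statement. An SAP could add detail, but the protocol's wording would still promise a protection that the named method does not give.

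Ordinary GEE solves equations whose mean is zero when the chance of being observed does not depend on the outcomes, given the model covariates. If someone with a poor 6-week score is less likely to return at 3 months, the data can be missing at random (the 6-week score is on file), yet the observed 3-month scores are a selected set. GEE recovers the right mean only so far as its working correlation carries the 6-week information forward correctly. A t-test at 3 months uses none of it.

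The Introduction says the findings will inform a full trial, and preliminary efficacy is a listed aim. A spurious difference of one or two tenths of an SD would feed into that design. The planned dropout check would not reveal it, because it looks at baseline values and not at the 6-week score.

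**Working it through.** **The plan's own figure.** The target follows from the cited audit, "the median sample size with continuous outcome measures to be 30 participants per group": 2 × 30 = 60. No power formula, SD or dropout rate lies behind it, so none can be taken from the document.

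**Assumptions, none from the protocol.** Three normal visits with SD 1; no true effect; missing data only at 3 months; true within-person correlations either 0.6 throughout, or 0.5 (baseline to 6 weeks), 0.3 (baseline to 3 months) and 0.7 (6 weeks to 3 months). Dropout in BA follows logit(p) = -1 + 1.5 × (6-week score). In TAU it is either flat, logit(p) = -1, or follows the opposite slope. A negative difference favours BA.

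**Step 1: t-test, or GEE with independence.** With separate means for each arm and visit, both estimate the difference in observed 3-month means, so

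bias = ρ(6 weeks, 3 months) × [E(6-week score | observed, BA) − E(6-week score | observed, TAU)].

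- Integrating the BA rule over a standard normal gives 33% missing and E(6-week score | observed) = -0.356. Flat TAU gives 1/(1 + e) = 27% missing and a mean of 0.
- BA-only rule: 0.6 × (-0.356) = -0.21 SD; 0.7 × (-0.356) = -0.25 SD.
- Opposite rules: 0.6 × (-0.712) = -0.43 SD; 0.7 × (-0.712) = -0.50 SD.
- Same rule in both arms: the two means cancel and the bias is 0.
- A milder rule (18% and 22% missing, correlation 0.6) gives -0.11 SD for BA only and -0.23 SD for opposite rules.

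**Step 2: GEE with the correlation estimated from the data.** Simulation with 400,000 per arm under the Step 1 rules; repeat runs differ by up to about 0.01 SD.

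| Working correlation | True 0.6, BA only | True 0.6, opposite | True 0.5/0.3/0.7, BA only | True 0.5/0.3/0.7, opposite |
|---|---|---|---|---|
| Independence | -0.21 | -0.43 | -0.25 | -0.50 |
| Exchangeable, fitted | about 0 | -0.01 to -0.02 | -0.07 to -0.08 | -0.16 to -0.17 |
| Unstructured, fitted | about -0.01 | -0.05 to -0.06 | -0.01 to -0.02 | about -0.05 |

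With the same rule in both arms, every structure gives about 0. The unstructured row is not exactly 0 because its correlations are estimated from residuals that dropout has already distorted.

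**Step 3: a real effect and lighter dropout.** With a true effect of -0.5 SD, 16–21% missing, a slope of 1 per SD and true correlations 0.5/0.3/0.7, the biases for the same rule, BA-only and opposite rules are:

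- independence: +0.04, -0.09 and -0.25
- exchangeable: +0.01, -0.04 and -0.08
- unstructured: within about 0.02 throughout.

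So a real effect can bring in some bias even when both arms share one rule.

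**Step 4: scale.** With 30 complete per arm, the standard error of an arm difference is √(2/30) = 0.26 SD. A bias of 0.16 SD is about 0.6 of one standard error.

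**The case against.** Several points on the other side stand.

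- The word *accommodate* may mean only that GEE uses every observed visit and does not need complete cases. That is true, but it is not what naming the missing-at-random mechanism conveys.
- The largest figures need an independence structure. The protocol does not name one, and a sentence that stresses correlated repeated data does not suggest it. A fitted structure removes much of the bias, often nearly all. For the GEE this stands; the t-tests gain nothing from it.
- The dropout rates and slopes are assumptions, and collecting outcomes from those who discontinue will reduce missingness. Both are correct.
- Working correlation, weighting and imputation are usual SAP content. Their absence from the protocol is therefore no fault; the fault is the unconditional claim.

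Three stronger readings are tempting, and the document does not support them.

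- A reader might infer that outcome-related dropout *will* bias the effect. It need not: the bias is about 0 when there is no effect and dropout acts alike in both arms.
- A reader might infer from the retention sentence that dropout must differ by arm, since TAU does not receive BA. The sentence concerns delivery by the regular clinician and low burden, and it fixes no direction. If BA helped retention, TAU would lose more, which is not the pattern illustrated here.
- A reader might infer that the standard errors are too small. That does not follow from the missing-data sentence, and it presupposes an uncorrected sandwich variance, which the protocol does not specify. Even then it is modest. On complete data the ratio is √(29/30) = 0.983, with type I error 5.9%. Simulated standard errors were 2–4% too small, and the 2-df arm-by-time test rejected about 6.5–7.1% of the time at a nominal 5%.

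**Conclusion.** The missing-at-random claim is wrong as a general statement about unweighted GEE, and nothing in the protocol makes it right. The visit-level t-tests fall outside any such protection. Under the stated assumptions (no true effect, 27–33% missing at 3 months), the spurious 3-month difference is about 0 to -0.17 SD for GEE with a fitted exchangeable structure. For independence, and for the t-tests, it is -0.2 to -0.5 SD. It is about 0 with like dropout in both arms, and within about 0.06 SD for a fitted unstructured correlation. Lighter dropout, or success in following up those who discontinue, shrinks all of these.

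This is a should-fix point. The effects are labelled preliminary, the trial disclaims power, and the feasibility proportions are untouched.

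**What to change.** In order of preference:

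1. Analyse the three time points with a likelihood-based repeated-measures mixed model: REML, unstructured covariance, Satterthwaite degrees of freedom (SPSS MIXED). Take the 6-week and 3-month arm contrasts, with intervals, from that model in place of the t-tests. This is valid under missing at random if the model is adequate.
2. Keep the GEE, but combine it with multiple imputation by arm or inverse-probability weights, and take the visit contrasts from the same analysis. A small-sample variance correction is then advisable, as a secondary matter.
3. Failing both, replace the claim with a statement that the plain GEE and the t-tests assume data missing completely at random, or missing depending only on model covariates.

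The cost is a sentence or two of analysis wording. The first option needs no new data or software, and its intervals will be slightly wider.

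### The 6-week and 3-month between-arm comparisons are unadjusted t-tests run only after a significant overall GEE effect, in a pilot not powered for significance

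*Protocol*

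**What the plan says.** All analysis statements are in the protocol, Data analysis, under Statistical analyses.

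- The preliminary effects of BA are analysed by GEE over "three points (baseline, and 6-weeks and 3-months after intervention) following the intention-to-treat principle, and relevant effect sizes will be calculated". Baseline is therefore one of the GEE time points, and the effect sizes carry no significance condition.
- On missing data: "The GEE analysis will account for intra-correlated repeated outcome data and accommodate data missing at random". Nothing comparable is said about any other test.
- For the separate follow-up visits: "T-tests will be carried out to examine any significant statistical differences between the two arms on primary and secondary outcome measures", carried out "at both follow-up measurements if the statistical significance of the overall treatment effect was found in the GEE analysis". No baseline covariate is named. The significance level is 0.05 throughout.
- The model terms behind the overall treatment effect are not given.

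The Sample size section sets 60 participants (30 per group), says that this figure "is not intended to be sufficiently powered to detect statistically significant differences in outcomes between groups", and gives its purpose as informing the size of a full-scale trial. The section on preliminary intervention effects has every outcome measured at baseline, at 6 weeks and at 3 months post-intervention. Study aim and objectives lists preliminary efficacy among the additional aims, after four feasibility objectives.

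**The concern.** A pilot that is meant to size a later trial should give an estimate with its uncertainty for each outcome at each follow-up, whatever the p-value. This plan makes the explicit visit comparisons depend on a significance test that the same protocol says it is not powered for. Three things follow.

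- Comparisons that appear only after a significant result are selected for being large. A full trial planned on them would be too small.
- The t-tests leave out a baseline score that is collected for every outcome, so they are less precise than the data allow.
- Where a visit value is missing, the t-test drops that participant and does not carry the missing-at-random handling claimed for the GEE.

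**Working it through.** **The plan's own figure.** 2 × 30 = 60 is consistent. It comes from pilot-size guidance; no effect size, SD or power is stated, so no power formula can reproduce it.

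**Inputs.** From the protocol: 30 per arm, three time points, level 0.05. Assumed, because the protocol gives no values: two-sided tests, SD 1 at each point, a common correlation ρ of 0.3, 0.5 or 0.7 between points, and the same true standardised difference d (0.3 or 0.5) at both follow-ups.

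**1. Precision.** The variance of the visit difference is 2/n for the t-test and 2(1 − ρ²)/n with baseline adjustment, a ratio of 1/(1 − ρ²). The 95% CI half-width of the t-test is t(0.975, 58) × √(2/30) = 0.52 SD. With adjustment it is t(0.975, 57) × √[(2/30)(1 − ρ²)(1 + 1/56)]. To match the adjusted variance, the t-test needs 30/(1 − ρ²) per arm.

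| ρ | Variance ratio | Half-width, t-test | Half-width, adjusted | Per arm for the t-test to match |
|---|---|---|---|---|
| 0.3 | 1/0.91 = 1.10 | 0.52 | 0.50 | 33 |
| 0.5 | 1/0.75 = 1.33 | 0.52 | 0.45 | 40 |
| 0.7 | 1/0.51 = 1.96 | 0.52 | 0.37 | 59 |

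At ρ = 0 there is no gain.

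**2. Selection by the gate.** There were 20,000 simulated trials per setting, with complete data. The main-effect gate tests the arm difference in the mean of all three points. The group-by-time gate tests the arm difference in the follow-up mean minus baseline. The table shows how often each gate is passed, and the mean 6-week difference among trials that pass.

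| True d | ρ | Main-effect gate: passed | Mean difference | Group-by-time gate: passed | Mean difference |
|---|---|---|---|---|---|
| 0.3 | 0.3 | 18% | 0.56 | 20% | 0.42 |
| 0.3 | 0.5 | 16% | 0.61 | 26% | 0.39 |
| 0.3 | 0.7 | 14% | 0.65 | 40% | 0.35 |
| 0.5 | 0.3 | 41% | 0.68 | 46% | 0.58 |
| 0.5 | 0.5 | 34% | 0.72 | 60% | 0.55 |
| 0.5 | 0.7 | 30% | 0.76 | 81% | 0.52 |

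For d = 0.3 the inflation is 0.35/0.30 = 1.2 to 0.42/0.30 = 1.4 times under the group-by-time reading, and 0.56/0.30 = 1.9 to 0.65/0.30 = 2.2 times under the main-effect reading. Required sample size goes as 1/d². A full trial sized on these gated differences would therefore have (0.30/0.42)² = 51% to (0.30/0.35)² = 73% of the participants it needs under the first reading, and (0.30/0.65)² = 21% to (0.30/0.56)² = 29% under the second.

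**3. Baseline within the overall effect.** If the overall effect is a group main effect over three points, d = 0.5 at both follow-ups becomes (0 + 0.5 + 0.5)/3 = 0.33, because the true effect at baseline is zero. If it is a group-by-time effect, baseline is the reference and nothing is diluted.

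**4. Missing visits.** This illustration assumes no true effect. Suppose the 20% most severe at baseline are lost from the BA arm and a random 20% from TAU. The mean baseline of those left in the BA arm is −φ(0.842)/0.8 = −0.350 SD, where φ is the standard normal density. The follow-up t-test is then biased by −0.350ρ: about −0.17 SD at ρ = 0.5 and −0.24 SD at ρ = 0.7, as a large simulation also showed. The baseline-adjusted difference was 0.00 in both cases.

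**The case against.** The strongest reply is that the GEE, not the t-test, is the effect analysis. It uses the baseline scores, and its effect sizes are to be calculated without a significance condition. A GEE with a group-by-time term could itself supply visit contrasts. The gate also gives some type I error protection within an outcome, and no feasibility objective depends on the t-tests. This stands, and it limits the severity. It does not justify the gated, unadjusted t-tests, which are the only visit-by-visit comparison that the protocol spells out.

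Four stronger readings are tempting, but the document does not support them.

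- A reader might infer that the t-tests are confined to completers and break intention to treat. Under Data collection and management, with participants' permission, "all outcome data will be collected and analysed from participants who discontinue the study or deviate from the intervention protocol". The tests are available-case and can compare participants as randomised. The narrower point about missing visits is what holds.
- A reader might take the dilution to 0.33 as a fact of the plan, or conclude that the visit comparisons will probably never appear. Both depend on the main-effect reading of an undefined term. Under the group-by-time reading with d = 0.5, the t-tests are run in 60% and 81% of trials at ρ = 0.5 and 0.7.
- A reader might compute inflation among t-tests that are themselves significant. The plan's condition is the GEE result, so only the gate figures above apply.
- A reader might suppose that the baseline tests replace baseline adjustment. Their only stated purpose is "to assess the homogeneity of the two groups", and nothing links them to the effect analysis.

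**Conclusion.** The point holds for the gated follow-up t-tests, at moderate severity. Their variance is 1.10 to 1.96 times that of a baseline-adjusted comparison for ρ from 0.3 to 0.7. Gating inflates the differences shown under either reading of the overall effect, by about 1.2 to 1.4 times or 1.9 to 2.2 times at d = 0.3. The bias from missing visits depends on who is lost and is zero if nobody is; the protocol states no dropout rate.

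The size of each effect rests on the assumed ρ and d, on equal correlations and on equal effects at both follow-ups. The conflict between a significance gate and a trial that disclaims power for significance rests on the text alone. Severity stops at moderate because efficacy is an additional aim and the GEE effect sizes are ungated.

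**What to change.** - Fit one longitudinal model (GEE) per outcome, with the 6-week and 3-month scores as outcomes and arm, visit, arm-by-visit and baseline score as terms. This also settles what the treatment effect is and takes baseline out of the outcome vector.
- For every outcome, report the baseline-adjusted difference at each follow-up with its 95% CI and standardised effect size, whatever the p-value.
- Delete the significance gate and the follow-up t-tests.

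The cost is a change of analysis wording; no new data, visits or participants are needed. Two things are given up. There is no longer a stand-alone claim of significance at a given visit, which the Sample size section does not seek. A participant with neither follow-up contributes no outcome to this model, so the number in that position should be reported by arm.
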